## Abstract

**Background:**

Persistent pain is a common yet debilitating complication after breast cancer surgery. Given the pervasive effects of this pain disorder on the patient and healthcare system, post-mastectomy pain syndrome (PMPS) is becoming a larger population health problem, especially as the prognosis and survivorship of breast cancer increases. Interventions that prevent persistent pain after breast surgery are needed to improve the quality of life of breast cancer survivors. An intraoperative intravenous lidocaine infusion has emerged as a potential intervention to decrease the incidence of PMPS. We aim to determine the definitive effects of this intervention in patients undergoing breast cancer surgery.

**Methods:**

PLAN will be a multicenter, parallel-group, blinded, 1:1 randomized, placebo-controlled trial of 1,602 patients undergoing breast cancer surgery. Adult patients scheduled for a lumpectomy or mastectomy will be randomized to receive an intravenous 2% lidocaine bolus of 1.5 mg/kg with induction of anesthesia, followed by a 2.0 mg/kg/h infusion until the end of surgery, or placebo solution (normal saline) at the same volume. The primary outcome will be the incidence of persistent pain at 3 months. Secondary outcomes include the incidence of pain and opioid consumption at 1 h, 1–3 days, and 12 months after surgery, as well as emotional, physical, and functional parameters, and cost-effectiveness.

**Discussion:**

This trial aims to provide definitive evidence on an intervention that could potentially prevent persistent pain after breast cancer surgery. If this trial is successful, lidocaine infusion would be integrated as standard of care in breast cancer management. This inexpensive, widely available, and easily administered intervention has the potential to reduce pain and suffering in an already afflicted patient population, decrease the substantial costs of chronic pain management, potentially decrease opioid use, and improve the quality of life in patients.

**Trial registration:**

This trial has been registered on clinicaltrials.gov (NCT04874038, [name]. Date of registration: May 5, 2021).

**Supplementary Information:**

The online version contains supplementary material available at 10.1186/s13063-024-08151-4.

## Background

### Persistent pain after breast cancer surgery

Breast cancer is the most commonly diagnosed cancer globally (2.3 million cases annually; ~ 12% of cancer diagnoses) [1] and the second most common type of cancer diagnosed in Canada (28,000 cases annually), despite it almost exclusively affecting females [2]. Fortunately, advances in cancer screening and management have substantially improved its prognosis, leading to a 85-90% 5-year survival rate in developed countries [1]. Increased survivorship has led, however, to the identification of important and problematic long-term complications from breast cancer management, specifically the devastating effects of persistent pain.

Breast cancer surgery is a critical component to breast cancer treatment. A common, yet vastly under-recognized complication after breast cancer surgery, including mastectomy and segmental mastectomy (lumpectomy), is persistent pain, often referred to as post-mastectomy pain syndrome (PMPS). PMPS is pain around the surgical incision (axilla, medial arm, shoulder, or chest wall on the side of surgery) that does not resolve, or worsens, ≥ 3 months after surgery (time needed to heal from a surgical incision) [3–5]. Unfortunately, breast cancer surgery has one of the highest rates of persistent pain among all surgical sub-types [6, 7]. In a recent systematic review of patients undergoing breast cancer surgery (146 studies, *n* = 137,675), the prevalence of persistent pain after breast cancer surgery was 35% (95% confidence interval [CI] 32 to 39%) [8]. Further, 20% of patients with persistent postsurgical pain report that their pain is moderate to severe in intensity (numeric rating scale [NRS] ≥ 4) [8–10]. Persistent pain after breast cancer surgery is chronic—over 50% of those afflicted will continue to suffer from it 7–12 years after surgery [11]. These are staggering statistics given that > 22,000 Canadians undergo breast cancer surgery each year [2] and younger patients (< 40 years) are at greater risk of this complication [12]. Persistent pain has a tremendous impact on quality of life as it causes emotional distress, mood disturbance, impaired sleep, and reduced physical functioning [13–16]. These deleterious effects of PMPS are experienced at a societal level through direct (healthcare costs) and indirect (loss of productivity) expenses, totaling $1 billion USD a year in the USA alone [17].

Although the pathophysiology of PMPS is not fully understood and likely multifactorial in nature, the inciting event may be related to neuronal injuries during surgical resection of cancerous tissue [4, 12, 18–21]. When peripheral nerves are injured, particularly nerves involved in pain transmission (A-δ and C-fibers), they respond with a barrage of neurochemical discharges [22, 23]. Given the rich innervation of the breast tissue and chest wall with peripheral nerves, trauma to these nerves during the perioperative care can initiate peripheral neuroplastic changes that ultimately lead to upregulation of pain receptors and mediators along the central nervous system (central sensitization), which is a requirement in the development of persistent and refractory pain [24].

### Intravenous lidocaine infusions

Intravenous lidocaine has been used in the treatment for acute pain, cancer pain, neuropathic pain, complex regional pain syndrome, and diabetic neuropathy [25–30]. Lidocaine infusions provide long-term analgesic benefits months after infusion cessation, suggesting a possible reversal effect within the peripheral and central nervous system [31]. While systemic lidocaine can *reverse* neuroplastic pain changes, whether it can be used to *prevent* persistent pain before it occurs is unknown. There is growing evidence to support this hypothesis [32–36]. In various animal models, lidocaine prevents the generation of spontaneous pain signals and the development of peripheral and central pain sensitization [37–39]. A recent meta-analysis of perioperative lidocaine infusion in noncardiac surgeries (6 including 4 in breast cancer surgery, *n* = 420) found that lidocaine significantly reduced the prevalence of chronic postsurgical pain (≥ 3 months after surgery; 101 events; odds ratio [OR] 0.29; 95% CI 0.18 − 0.48; *I*^2^ = 0%) [40]. In addition, IV lidocaine infusion has been explored widely for improved postoperative pain and accelerated recovery after gastrointestinal surgeries [31, 41–46].

Prior RCTs have examined the effect of an intraoperative lidocaine infusion on persistent pain after breast cancer surgery. In a systematic review (97 patients), intraoperative lidocaine compared to placebo significantly reduced persistent pain 3 to 6 months after breast cancer surgery (23 events; relative risk [RR] 0.33; 95% CI 0.14−0.78) [47]. Results from the 3 RCTs published since this review are in line with these results [36, 48, 49]. Kim et al. (78 patients) showed that intraoperative lidocaine decreased pain scores at 3 months after surgery (McGill pain questionnaire 8.9 vs. 12.7, *p* = 0.046) [34]. Kendall et al. (150 patients) found that intraoperative lidocaine decreased the proportion of patients who reported pain attributable to surgery at 6 months after surgery (13% vs. 29%, *p* = 0.04); however, they did not find a difference at 3 months [49]. Similarly, we carried out a pilot RCT (100 patients) demonstrating that lidocaine reduced the development of persistent pain at 3 months by 32% (43% vs. 63%; RR 0.68, 95% CI 0.47 to 1.0; *p* = 0.049) [36]. The small sample sizes in the above RCTs are at risk of chance findings, overestimation of treatment effects, fragility, and limitations in exploring important secondary outcomes such as safety, persistent opioid use, function, and quality of life [40, 50]. Further, these trials were typically conducted at single institutions, limiting generalizability. Lidocaine infusions are a promising intervention to reduce persistent pain after breast cancer surgery; however, before widespread use can be recommended, a large, multicenter, RCT is needed to definitively determine its efficacy.

Following our recently published pilot trial demonstrating feasibility, we propose to undertake a Canadian-led, multicenter, international, blinded, randomized, placebo-controlled trial to determine the definitive effects of an intraoperative lidocaine infusion in 1602 patients undergoing breast cancer surgery. This trial is the Prevention of persistent pain with LidocAine iNfusions in breast cancer surgery (PLAN) trial. We used the SPIRIT checklist when writing our report (See Fig. 1) [51].

**Fig. 1 Fig1:**
[figure not shown]
Trial schedule of enrolment, interventions, and assessments

## Methods

### Trial design

PLAN will be a multicenter, parallel-group, blinded, 1:1 randomized, placebo-controlled, superiority trial of 1602 patients undergoing breast cancer surgery.

### Trial objectives

#### Primary objective

The primary objective of this trial is to determine the effect of an intraoperative intravenous (IV) lidocaine infusion on reducing the development of persistent pain 3 months after breast cancer surgery.

#### Secondary objectives

Secondary objectives of this trial are to measure the effect of IV lidocaine, compared to placebo, on:Pain intensities (NRS 0-10) at rest and movement on postoperative days (PODs) 1–3;Oral morphine-equivalent opioid consumption on POD 1–3, 3 months, and 1 year after surgery;Persistent pain at 1 year after surgery;Moderate-to-severe persistent pain (NRS ≥ 4 at rest) at 3 months and 1 year after surgery;Persistent neuropathic pain (defined by Douleur Neuropathique 4 [DN4] symptoms assessment) at 3 and 12 months after surgery;Sensory and affective qualities of pain (Short Form McGill Pain Questionnaire 2) at 3 months and 1 year after surgery;Emotional functioning (Profile of Mood States [POMS]) at 3 months and 1 year after surgery;Physical functioning (Brief Pain Inventory [BPI]) at 3 months and 1 year after surgery;Quality of life (EQ-5D-5L) at 3 months and 1 year after surgery;Cancer recurrence at 12 months;Adverse events; adverse drug related events within 24 h of infusion and serious adverse events throughout the trial conduct;Cost-effectiveness.

## Participants, interventions, and outcomes

### Study setting

Patients are currently recruited from academic and community hospitals across Canada using a convenience sample of those undergoing breast cancer surgery. Additional international centers are being evaluated to join as recruitment centers to improve generalizability of results.

### Eligibility criteria

#### Inclusion criteria

Age ≥ 18 years old; andUndergoing a unilateral or bilateral lumpectomy or mastectomy, inclusive of all pathologies, including prophylactic surgery (e.g., family history or BRCA gene mutation).

#### Exclusion criteria

Previous breast surgery within 6 months of index surgery;Undergoing any autologous flap procedure during index surgery;Presence of known chronic pain disorder involving surgical site or ipsilateral chest wall, shoulder, or arm during the 3 months prior to index surgery;Documented hypersensitivity or allergy to lidocaine;Surgery not planned to be performed under general anesthesia and/or planned use of regional or neuraxial anesthetic techniques before surgery (i.e., epidural, paravertebral, serratus plane block, pectoralis or modified pectoralis block);History of ventricular tachycardia, ventricular fibrillation, or atrioventricular block without a pacemaker;Known cirrhotic liver disease;Pregnant; orUnlikely to comply with follow-up (e.g., no fixed address, language difficulties that would impede valid completion of questionnaires, plans to move out of town).

### Randomization

A statistician not involved in the study analysis will generate an online encrypted randomization list. Randomization will use permuted blocks of varying size and will be stratified by center and breast reconstruction (i.e., immediate reconstruction surgery with implants at the time of index surgery). Patients will be randomized in a 1:1 ratio between lidocaine and placebo. Research assistants (RAs) will randomize patients through an online 24-h, interactive, web-based randomization system. Randomization will occur on the day of surgery to minimize the risk of surgery being postponed or cancelled after randomization. For cases performed first thing in the morning, if needed patients could be randomized the night before.

### Blinding

In addition to randomization, we will blind patients, healthcare providers, research assistants, data collectors, investigators, and outcome adjudicators to treatment allocation using blinded study medications. RAs randomizing a patient will receive a unique ID (patient study number) and an encrypted code corresponding to a study medication on the master randomization list. A designated pharmacist at each study center will have access to the master randomization list with encrypted codes and will prepare either a 50-mL syringe of 2% lidocaine or 0.9% normal saline solution. All syringes will be blinded and will indicate study information, the encrypted code and that the enclosed solution is a 2% (or 20 mg/mL) concentration (ensuring equivalent volumes are administered in both treatment groups). The study pharmacist at each participating site will be instructed on the importance of not sharing the blinded allocation data with anyone and will sign a form indicating that they will keep this information confidential.

### Description of study interventions

A study team member (RA or pharmacist) will provide anesthesiologists with study medications for administration. Patients in the intervention group will receive an IV lidocaine infusion using a dosage regimen of 1.5 mg/kg bolus of a 2% lidocaine solution with induction of general anesthesia followed by a 2.0 mg/kg/h infusion until the end of surgery (and up to 30 min in the recovery room). Patients in the control group will receive a placebo bolus and infusion with normal saline (0.9% sodium chloride solution) at the same rate. Study medications will be prepared in blinded 50-mL syringes and labelled as per Health Canada requirements. Total body weight is used for the bolus and infusion dosage calculation. If a patient’s total body weight is over 100 kg, a weight of 100 kg can be used in the calculation, at the discretion of the attending anesthesiologist.

There are no modifications to study infusion regimen allowed. However, if the clinician team suspects a case of local anesthetic toxicity, then the care team can stop the infusion at their discretion and treat the patient according to standard clinical practice guidelines.

Given that study medications are administered by the attending anesthesiologist, compliance with study interventions will be high. In our pilot trial, we had a 94% compliance rate. To ensure compliance with study drug administration in this definitive trial, we have educated the anesthesia and surgical groups at each site through department and grand rounds presentations, provided posters within the operating room, sent reminder emails the day prior for the surgeon and anesthesiologists caring for the included patients, and have our research team present for the start of the surgical case to remind and ensure study medications are being administered.

### Concomitant care

Study patients will be restricted on any additional IV or regional local anesthetic to control the risk of overdose and confounding treatment effects and intraoperative wound infiltration will be limited to 50 mg of a long-acting local anesthetic (i.e., bupivacaine or ropivacaine). Otherwise, intraoperative and postoperative pain management plans will be left to the discretion of the attending clinicians. Our large sample size should balance variations in practices across treatment groups.

### Outcomes

#### Primary outcome

Our primary outcome, persistent pain at 3 months, is informed by the definition for chronic postsurgical pain established by the International Association for the Study of Pain (IASP) [5]. A patient will meet the primary outcome if (1) the patient reports non-zero pain (NRS pain score > 0 at rest) within the last 7 days, (2) located around the surgical incision (i.e., axilla, medial arm, shoulder, or chest wall on the side of surgery), (3) at 3 months after surgery (IASP’s time required for normal healing from injury), (4) with no other identifiable cause of pain (e.g., no pre-existing pain condition, infection, or malignancy).

The NRS scale used in criterion 1 is an 11-point scale where 0 is “no pain” and 10 is “worst possible pain”. Criteria 4 is met by excluding patients with known preoperative pain in the area of their surgery (exclusion criteria) and those with any current or previous (within 1 month of assessment) surgical site infections or known cancer recurrence. If any infections or recurrence is suspected during follow-up, RAs will review with their respective Site Principal Investigator (PI) and send the patient’s medical records to the Anesthesia Clinical Trials Unit (ACTU). If needed, adjudication by two independent investigators blinded to the patient’s treatment allocation will be performed.

#### Secondary outcomes

Study personnel will follow patients (1 h into recovery room stay, PODs 1–3) and ensure the following secondary outcomes are collected, including from the patient’s medical record and pain diary: oral morphine-equivalent opioid consumption; NRS pain scores at rest and movement (taken once in recovery and twice a day [morning and evening] on PODs 1–3); and time to recovery room and hospital discharge. Pain intensity ratings on movement will be assessed by asking the patient to abduct their arm 90° on the ipsilateral side of surgery.

One of the secondary outcomes includes persistent pain at 12 months, which will be assessed using the same criteria as the primary outcome but at 12 months. Moderate-to-severe persistent pain is a binary outcome measured at 3 and 12 months defined as persistent pain with an NRS pain score of ≥ 4 at rest 24 hours before evaluation. Similarly, persistent neuropathic pain is a binary outcome defined as persistent pain at 3 or 12 months that involves neuropathic pain as indicated by the DN4 interview, a validated instrument to detect neuropathic pain [52]. The original DN4 questionnaire required a patient examination but the DN4-interview only requires self-reported data. Patients who meet the criteria for persistent pain at 3 or 12 months after surgery report on the sensory and affective qualities of their pain using the SF-MPQ-2, a reliable tool to evaluate pain in those with chronic pain. It has been validated in a breast cancer population and has been used in several analgesic trials after breast cancer surgery [53–56].

Additionally, all patients will be asked about their emotional and physical functioning, and their quality of life at the 3- and 12-month follow-up. Emotional functioning will be evaluated using the POMS, which is a reliable instrument, validated in a breast cancer population to evaluate aspects of psychological distress (e.g., depression, anxiety, anger) [57]. Physical functioning will be measured by the interference scale of the BPI, which provides a reliable and valid assessment of interference of pain on level of functioning and has been used in a variety of post-mastectomy pain trials [58–60] and in patients with breast cancer pain [61–64]. Given the well-established inverse relationship between pain and quality of life [65, 66], we will use the EQ-5D-5L [67], which is a widely used measurement tool for assessing health-related quality of life [68]. This instrument is also commonly used in health economic evaluations, which will be explored if lidocaine infusions are shown to be significant for the primary outcome.

Cancer recurrence will be assessed at 3 and 12 months. If cancer recurrence is suspected during follow-up, RAs will review with their respective Site Principal Investigator (PI) and send relevant source documents to the coordinating center. If needed, this outcome will be sent for adjudication by two independent investigators blinded to the patient’s treatment allocation.

Adverse events (AE) will be monitored as a secondary safety outcome. Adverse events will be defined as “any noxious and unintended response to an Investigation Medicinal Product (IMP) related to any dose.” Given the half-life of lidocaine is approximately 90 min, screening for adverse events will be limited to the period of administration (intraoperative period), and immediate postoperative period (up to 24 h after surgery). AEs will be screened and reported by the attending anesthesiologists administering study medications intraoperatively and by RAs reviewing postoperative medical records. Serious adverse events (SAEs) will be monitored throughout the entire trial conduct.

Cost-effectiveness will be assessed if lidocaine significantly reduces persistent pain at 3 months to determine cost-savings from a patient and societal perspective if lidocaine is adopted widely into practice.

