### Sample size

Only a few prospective studies provide data on the prevalence of persistent pain at 3 months after breast cancer surgery, with estimates ranging from 33 to 82% [32, 34, 49, 73, 74]. The largest study (*n* = 150) reported a 33% prevalence at 3 months; however, only 84 (56%) patients provided follow-up data. Our pilot (*n* = 100), conducted at two Canadian centers, found a prevalence of persistent pain of 58.3% (95% CI 38.6 to 78.1%) in the control group at 3 months. Furthermore, our pilot found a 32% relative risk reduction (RRR) with the use of IV lidocaine, whereas Grigoras et al. [32] and Kim et al. [34] found a 75 and a 50% RRR at 3 months, respectively. We believe these RRR estimates are likely overestimations of the true treatment effect given the small size of the trials, the multiple pathogenic mechanisms involved, and the rarity of such large effect sizes in the medical literature [75, 76] and within chronic pain prevention trials [77].

We have therefore chosen to design our trial to identify a plausible, but clinically important, 25% RRR while using 30% as the control group pain prevalence at 3 months. To achieve 90% power to detect in a two-sided comparison with *α* = 0.05, and 10% loss-to follow-up, we will need a sample of 1602 participants. For a fixed RRR, power increases as the control group prevalence increases. This sample size also provides adequate power to inform realistic RRRs in important but less common secondary outcomes such as presence of moderate-to-severe pain. For example, based on a control group prevalence of moderate-to-severe pain of 16% in our pilot, we have 80% power to detect a RRR of 31% or greater.

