### Analysis

A statistical analysis plan (SAP) has not yet been completed and approved by the Steering Committee. In general, the analysis of results will be completed in the following manner but is subject to minor changes in the SAP. Patients will be analyzed according to their allocated treatment group (intention-to-treat analysis). No imputations will be made for missing data. The relative risk for the primary outcome of the presence of persistent pain at 3 months will be estimated (along with its 95% CI) from a log-binomial model that includes factors for treatment group and the stratification variables (study center, breast reconstruction). If the number of centers is large, a center will be represented by a random effect [78]. A similar analytical approach will be used for secondary binary outcomes. Treatment effects will also be quantified by calculating absolute differences between intervention groups. Analyses of continuous variables such as acute pain NRS scores at rest and movement, oral morphine-equivalent opioid consumption, time to hospital discharge, scores on SF-MPQ-2, POMS, BPI, and EQ-5D-5L will use linear regression (with transformations of outcomes if necessary) to estimate treatment effects and their 95% CIs, again with factors (or random effects) for stratification variables. Baseline characteristics in each group will be summarized without any comparative analyses. If more than 5% of participants are missing the primary outcome, the primary analysis will combine results across multiple imputed datasets, generated from a regression model using other available pain measurements. Analysis of adverse events will be summarized using count and proportions in each intervention group (lidocaine and placebo groups) and numerical values will be used for exploratory analysis between groups. All statistical analyses will be performed using the R statistical language.

Analysis of trial outcomes will be completed at the end of the trial. There will be no interim analysis for efficacy due to the possibility of introducing bias and over-estimating treatment effects [79–81].

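### SF-MPQ-2 is collected only from patients with persistent pain but analysed as a lidocaine effect, so the comparison is not randomized and its bias can run either way

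*Protocol article*

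**What the plan says.** All references are to the protocol article.

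- **Secondary objectives** lists, among effects of lidocaine compared with placebo, "Sensory and affective qualities of pain (Short Form McGill Pain Questionnaire 2) at 3 months and 1 year after surgery".
- **Secondary outcomes** says who completes it: "Patients who meet the criteria for persistent pain at 3 or 12 months after surgery report on the sensory and affective qualities" of their pain. The next paragraph turns to the other instruments: "Additionally, all patients will be asked about their emotional and physical functioning, and their quality of life at the 3- and 12-month follow-up". Read together, these give POMS, BPI and EQ-5D-5L to everyone and the SF-MPQ-2 to a subset. The word "only" is not in the text, but no other reading fits.
- **Primary outcome** fixes entry to the subset. The first criterion is that "the patient reports non-zero pain (NRS pain score > 0 at rest) within the last 7 days". The others concern location, timing and the absence of another cause.
- **Analysis** declares intention to treat, says "No imputations will be made for missing data" (with an exception for the primary outcome only), and states that "scores on SF-MPQ-2, POMS, BPI, and EQ-5D-5L will use linear regression" to estimate treatment effects with 95% confidence intervals.

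Nowhere does the article give pain-free patients an SF-MPQ-2 score, call the result descriptive, or say what the subset comparison estimates.

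**The concern.** Randomization makes the two arms comparable as a whole. It does not make the patients with persistent pain in one arm comparable with those in the other, because treatment may decide who is in that group. If lidocaine prevents some cases, the remaining lidocaine cases differ from the placebo cases by selection, even if no individual score changes. A regression of SF-MPQ-2 on treatment among cases then mixes any true effect on pain quality with this change in composition, and adjusting for centre and reconstruction does not separate them.

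At stake is a named secondary efficacy estimate with a confidence interval, reported beside estimates from all patients as if it had the same standing. It could point the wrong way in either direction. It also gives lidocaine no credit for pain that was prevented.

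**Working it through.** **Inputs from Sample size:** "25% RRR while using 30% as the control group pain prevalence at 3 months", hence 30% against 0.75 × 30% = 22.5%; 90% power; two-sided alpha 0.05; 10% loss; 1602 patients in total.

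**1. The plan's own figure.** With pooled rate 0.2625,

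n per arm = [1.96·√(2·0.2625·0.7375) + 1.2816·√(0.30·0.70 + 0.225·0.775)]² / 0.075² = 722.

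That is 1444 evaluable patients, and 1444/0.9 = 1605. The unpooled formula gives 1598. The stated 1602 lies between them and is reproduced.

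**2. Size of the SF-MPQ-2 comparison at 3 months.** Evaluable patients per arm: 1602 × 0.9 / 2 = 721. Cases: 721 × 0.30 = 216 on placebo and 721 × 0.225 = 162 on lidocaine. Together that is about 26% of evaluable patients.

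**3. Direction of the bias, in general.** Suppose lidocaine prevents pain in some patients and changes nobody else's score. Let A be the mean score of patients with pain under either treatment (22.5%) and P the mean score, under placebo, of those whose pain is prevented (7.5%).

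- Placebo cases: (0.225A + 0.075P)/0.30 = 0.75A + 0.25P
- Lidocaine cases: A
- Difference among cases (lidocaine minus placebo): 0.25(A − P)
- Difference among all patients, pain-free scored 0: 0.225A − 0.30(0.75A + 0.25P) = −0.075P

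So the cases-only difference is positive (apparent harm) if the prevented cases are milder than the rest, zero if equally severe, and negative if more severe. No patient is worse in any of these. With assumed means, A = 3.0:

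| P | Among cases | All patients |
|---|---|---|
| 1.0 | +0.50 | −0.075 |
| 2.0 | +0.25 | −0.15 |
| 3.0 | 0 | −0.225 |
| 4.0 | −0.25 | −0.30 |

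**4. Size in SD units.** Assumption: severity among placebo cases is a standard normal above its 70th percentile (0.524). Its mean is φ(0.524)/0.30 = 1.159 and its SD is 0.514.

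- *Only the mildest quarter prevented:* the remaining cases lie above the 77.5th percentile, with mean 1.333. Bias (1.333 − 1.159)/0.514 = **+0.34 SD**.
- *Prevention leaning toward milder cases* (probability averaging 25% and falling by 0.1 or 0.2 per latent SD): **+0.07 and +0.13 SD**.
- *Prevention at random:* **0**.
- *Only the severest quarter prevented:* the remaining cases lie between the 70th and 92.5th percentiles, with mean 0.916. Bias (0.916 − 1.159)/0.514 = **−0.47 SD**.

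In simulations with 721 per arm, the share of trials significant for harm was about 93% in the first case and about 9% to 21% in the second. In the last case, practically all trials were significant for benefit.

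**The case against.** **Size.** A reader might infer that the plan is set to report harm from a harmless drug, since one scenario gives significant harm in about 93% of trials. The documents do not support that. It needs lidocaine to remove exactly the mildest quarter of cases and do nothing else. The article gives no SF-MPQ-2 mean, SD or severity gradient, and the bias could equally favour lidocaine. The zero threshold on the pain scale admits very mild cases, which makes the harm direction plausible but does not establish it. This part of the objection stands.

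**Remedy.** Scoring non-cases 0 is not clean either.

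- Patients can miss the persistent-pain definition because of infection, recurrence, pain elsewhere or pain only on movement. They have no SF-MPQ-2 score, yet may have pain.
- With 70% to 78% zeros, a rank test mostly asks whether pain is present. In simulation, a Wilcoxon test gave the same significance verdict as the primary-outcome chi-square test in 97% of trials with random prevention and 98% with a general downward shift in pain.
- In the mildest-quarter scenario, the all-patient mean difference was only −0.02 SD, with 6% power.

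These points also stand, and they shape the fix.

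**Scope.** This is one of about a dozen secondary objectives. Moderate-to-severe pain, neuropathic pain, BPI, POMS and EQ-5D-5L cover severity and burden without this selection. That argues for lower urgency, not for leaving it.

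**The SAP.** The article says its SAP was not complete and could make minor changes, so a rule may yet be written. But the article does not leave the point open: it states both the restricted collection and the between-arm regression, and the two do not fit.

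**Conclusion.** The concern holds. As written, the SF-MPQ-2 regression compares groups selected on a post-randomization outcome that treatment is meant to change, so its estimate is not a randomized treatment effect. That follows from the text and rests on no distributional assumption.

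The amount of bias does rest on assumptions. Under truncated-normal severity and the design rates, it ranges from about +0.34 SD to −0.47 SD, with values near +0.1 SD if prevention merely leans toward milder cases and none if prevention is unrelated to severity. Neither a prediction of harm nor a single figure is justified. The 3-month rates supply the 216 and 162; the article gives no design rate for 1 year, where the same defect applies.

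It would also be too strong to infer a threat to the trial's main conclusion: the primary analysis and sample size are unaffected. This should be fixed before the data are unblinded.

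**What to change.** Remove SF-MPQ-2 among cases from the list of outcomes analysed by linear regression in Analysis. Report the scores by arm at 3 months and 1 year as description only, with no treatment-effect estimate, confidence interval or p-value, and say that the groups are selected on outcome. This costs wording only.

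If a between-arm comparison is still wanted:

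- Compare all randomized patients, assigning 0 only to those recorded as having no pain at the visit. State that this is a scoring rule, so that it does not clash with the no-imputation statement.
- Use a method suited to about 70% to 78% zeros, such as a proportional-odds or two-part model. In a two-part model, the part restricted to patients with pain should again be descriptive.
- Treat patients who have pain but do not meet the persistent-pain criteria as missing, not 0, or give them the questionnaire too. The second choice is a change in data collection and helps only for visits still to come.

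The price of this option is interpretation: the estimate reads as overall pain burden rather than pain quality, and it largely tracks the primary outcome. It should not be presented as independent support.
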